### Study population

The main target groups for analysis will be:

AOKN members who died in 2019;health care providers and experts at the micro level, including GPs; oncologists; pain medicine or palliative care specialists; geriatricians; and multi-disciplinary specialists from level 3 outpatient palliative care teams, nursing care services, nursing care facilities and inpatient hospices; andpalliative and hospice care stakeholders at the meso and macro levels, including representatives from the German Hospice and Palliative Care Association (Deutscher Hospiz- und Palliativverband), the German Association for Palliative Medicine (Deutsche Gesellschaft für Palliativmedizin), the Professional Association of specialised outpatient palliative care (Fachverband SAPV), other societies and professional associations, the Association of Statutory Health Insurance Physicians Lower Saxony (Kassenärztliche Vereinigung Niedersachsen), GP associations, the German Home Care and Nursing Society (Deutscher Pflegeverband e.V.), and health care insurance providers.

### Inclusion, exclusion and termination criteria

In phase 1, work package 1a, only secondary data will be analysed; thus, there will be no participant recruitment. Inclusion criteria will depend on the type of analysis (e.g. utilisation of level 2 outpatient palliative care or death). For deceased patients, the inclusion criteria will comprise: an age of 18 years or older at the time of death and continuous insurance during the year of death and the preceding calendar year.

In phase 1, work packages 1b and 1c, online surveys will be conducted with all registered GPs and all level 3 specialist outpatient palliative care teams in Lower Saxony. The aim will be to achieve a full assessment of both groups in this federal state. Therefore, no further inclusion or exclusion criteria will be needed. Each survey participant will independently decide whether to participate, as well as when to cease participation, if desired. No termination criteria will be defined.

In phase 2, work packages 2a and 2b, experts will participate in a workshop and/or Delphi survey. Participants will be selected according to the principle of diversity, in order to ensure the adequate representation of inpatient, ambulatory, generalist and specialist service providers and all interfaces with level 2 palliative care. The exclusion criteria will be comprised of insufficient German language skill and less than 1 year of experience in hospice and palliative care. Experts will be able to terminate their participation at any time.

### Data analysis

The data analysis will aim at describing the current state of level 2 outpatient palliative care administration, in practice, and determining consented recommendations for its optimisation and development. The analysis of secondary data from the AOKN in phase 1, work package 1a, will be carried out quantitatively and descriptively. Quantitative data from the surveys with GPs and specialist outpatient palliative care teams in work packages 1b and 1c will also be analysed descriptively, using IBM SPSS Statistics version 25 (SPSS Inc., Chicago, IL, USA).

Qualitative data from the expert workshop in phase 2, work package 2a, will be transcribed verbatim from the audio record by student assistants, and analysed qualitatively in MaxQDA (VERBI Software Consult Sozialforschung GmbH, 1989–2020), using the methodological principles of qualitative content analysis [13, 14]. The thematic characteristics of level 2 palliative care determined in previous study phases will comprise an a priori category system, which will be successively expanded with the workshop data.

Quantitative data from phase 2, work package 2b, will be processed in IBM SPSS Statistics 26 (SPSS Inc., Chicago, IL, USA). Recommendations from the first Delphi round that receive support from at least 80% of the participants (on the basis of the scale responses “I rather agree” and “I fully agree”) will be considered consented. Results will be calculated by means of a frequency analysis. Recommendations that are non-consented in Delphi round 1 will be revised according to any free text comments and subjected to a second Delphi round. This interim analysis and adaptation of the recommendations will take approximately 2–3 weeks. Following this, the revised recommendations will be sent to all participants who completed the first Delphi round for a second online evaluation. A third round will be applied, if necessary, following the same method.

### Data security

All personal data will be treated in accordance with the German General Data Protection Regulation. All data collected in the course of the study will be subject to confidentiality and all members of the project team will be bound to data secrecy. The data collected from all work packages will be anonymised and stored in accordance with the applicable data protection guidelines. Furthermore, they will be exclusively analysed with regard to the objectives stated in the project proposal. The quantitative survey data will be anonymised for the statistical analysis. The analysis of all qualitative data will be carried out in pseudonymised form (i.e. without the names of persons, institutions or locations). Recorded data will be deleted upon participants’ request, as long as the data have not yet been anonymised.

### Expected results

The project team assumes that: 1) health care providers and stakeholders will report different experiences, both positive and negative, with the provision of level 2 palliative care; 2) experience-based ideas from health care providers and stakeholders could contribute to optimising level 2 palliative care; and (3) the care of seriously ill patients in an outpatient setting could be improved by the empirical results of a systematic evaluation of the administration of level 2 palliative care.

The main expected results are as follows: 1) a multi-perspective overview of the extent and nature of the administration of level 2 outpatient palliative care in Lower Saxony and 2) a set of evidence-based recommendations for the needs-oriented development of level 2 palliative care in Germany.

### Ethical considerations

The consortium management has submitted the study protocol to the responsible ethics committee and made revisions in accordance with their advice. A positive ethics vote (N° 9629_BO_K_2021) for Polite was issued by the Ethics Committee of the Hannover Medical School on 23 February 2021. The data protection officer of the MHH and the AOKN confirmed that the study meets all data protection laws.

All participating health care providers and stakeholders from hospice and palliative care will be informed (verbally and in writing) in detail about the questionnaires and the aims and purpose of the project, in advance. Participation will only commence following participants’ express consent to participate in the online survey (phase 1, work packages 1b and 1c; phase 2, work package 2b) or give additional written informed consent (phase 1, work packages 1b and 1c; phase 2, work package 2a). Written information will be provided to all participants. Each participant will have the right to refuse or terminate participation at any time before or during the data collection, without giving a reason.

## Discussion

### Study risks

Access to health care providers and stakeholders in the field of hospice and palliative care can be difficult, depending on the attitudes and experiences of these parties with respect to scientific research. Thus, recruiting the intended number of participants in phase 1, work packages 1b and 1c, and phase 2, work packages 2a and 2b, may be methodologically difficult. However, there are several reasons to predict the successful application of the various work packages: 1) participation will require only a single (questionnaire, expert workshop) or a few short (Delphi survey) expenditures of time; 2) the target populations are not difficult to reach; 3) the target number of participants was calculated in accordance with the topics and research methods applied in the respective study phases; and 4) recruitment will take place throughout Lower Saxony in phase 1 and Germany in phase 2.

To achieve the target sample sizes, the project team will take the following actions, if necessary:

Phase 1:All registered GPs in phase 1, work package 1b, will be informed about the project and invited to participate in the survey, primarily via email and secondarily via letter or fax, if no email address is available.The survey invitation will be advertised in the ‘Ärzteblatt’ Lower Saxony, which is distributed to all registered physicians in Lower Saxony. GPs on existing mailing lists (e.g. for teaching practices at the Hannover Medical School) will also be contacted.All specialised palliative care teams in phase 1, work package 1c, will be informed about the project and invited to participate in the online survey via email or, in exceptional cases, via letter.The online questionnaires for work packages 1b and 1c will be accessible for at least 4 weeks, with weekly reminders sent via email.Phase 2:To encourage participation in the planned expert workshop in phase 2, work package 2a, participants will be compensated for their loss of working hours, travel costs to and from the workshop and overnight accommodation.To compensate for a possible low participation rate of 20–30% and an expected drop-out rate of 10% during the Delphi survey in phase 2, work package 2b, as many potential participants as possible will be informed and invited to participate.It is assumed that, based on their experiences with palliative care and health services research, participating health care providers and stakeholders will have a high intrinsic motivation to improve palliative care.The project team will respond to challenges in a timely manner, organising additional conference calls and project meetings, as needed.

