### Study phases and data collection

In phase 1, work package 1a, quantitative routinely collected data from the statutory health insurance provider Allgemeine Ortskrankenkassen Lower Saxony (AOKN) will be used to analyse the development of level 2 outpatient palliative care services over time and to identify patients who died in 2019 and received outpatient palliative care services (at any level). Sociodemographic and disease-related data for these patients will be collected and compared according to those who received level 2 palliative care versus those who received palliative care at levels 1 or 3. The consortium will reveal the care trajectories of these patients, the patients who received different forms of outpatient palliative care and the transitions that occurred between levels of outpatient palliative care. In addition, the use of health care services beyond palliative care (but alongside level 2 palliative care) will be examined from billing records; such services might include medical specialists or hospital admissions. These data are expected to reveal the extent to which level 2 palliative care is implemented. Finally, a comparison with data from patients deceased in 2017 will show on a macro level whether (and to what extent) the introduction of level 2 palliative care shifted the type and administration of palliative care at levels 1 or 3. The data required for this will be extracted and analysed by the AOKN.

In phase 1, work package 1b, a quantitative, standardised questionnaire for GPs will be developed on the basis of the literature, previous scientific findings, available political statements and contributions from relevant professional associations. The online survey will be sent to all (N = 5,158) GPs registered in Lower Saxony to collect information on the number and characteristics of physicians offering level 2 palliative care. A response rate of approximately 15% (n = 774) is expected.

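### Contacting GPs on existing mailing lists may tilt the state-wide GP survey figures; list status should be recorded before the survey opens

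*Protocol article*

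**What the plan says.** Under Study phases and data collection, the protocol article states that "The online survey will be sent to all (N = 5,158) GPs registered in Lower Saxony" and gives the purpose as "to collect information on the number and characteristics of physicians offering level 2 palliative care". On participation it says: "A response rate of approximately 15% (n = 774) is expected". Under Inclusion, exclusion and termination criteria, the ambition for the GP survey and the team survey is complete coverage: "The aim will be to achieve a full assessment of both groups in this federal state".

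The recruitment measures are listed under Study risks, introduced by "To achieve the target sample sizes, the project team will take the following actions, if necessary". For work package 1b, all GPs are invited "primarily via email and secondarily via letter or fax, if no email address is available", an advertisement goes into a journal distributed to every registered physician in the state, and weekly email reminders run while the questionnaire is open. Among these measures stands one of a different kind: "GPs on existing mailing lists (e.g. for teaching practices at the Hannover Medical School) will also be contacted".

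Under Data analysis, the article says: "Quantitative data from the surveys with GPs and specialist outpatient palliative care teams in work packages 1b and 1c will also be analysed descriptively". It neither mentions nor rules out weighting, and it does not say whether the recruitment route or list membership will be recorded. Data security states that the survey data are anonymised for analysis.

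**The concern.** The general invitation, the advertisement and the reminders are directed at the whole register. The list contact is directed at GPs who already have some tie, in the example given to the medical school running the study. Study risks itself says that access to providers depends on their attitudes to and experience of research. It is therefore plausible that these GPs answer more readily and that an extra prompt widens the gap. They may also differ in level 2 provision, since the Introduction says that only specially qualified GPs can offer it. That second step is plausible but not documented.

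If both hold, simple frequencies from work package 1b describe a mix of practices that differs from the register. This matters because the number of level 2 physicians is itself a survey aim, and because the Setting section expects the findings to carry over to Germany as a whole. Timing matters too: if list status is not captured when the anonymised survey is fielded, a later analysis plan may have no means of recovering it.

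**Working it through.** **The plan's own figure.** 5,158 × 0.15 = 773.7, which rounds to the stated 774. The expected response is reproduced.

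**Inputs from the article.** Register N = 5,158; overall response 0.15; n = 774.

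**Inputs assumed, because the article gives none.**
- s, the share of the register that is on the lists: 2%, 5% or 10% (about 103, 258 or 516 GPs).
- r, the response among listed GPs: 15%, 20%, 30% or 45%.
- d, the difference in the proportion offering level 2 between listed and other GPs: 10, 20 or 30 percentage points.

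**Formulas**, with overall response held at 15%:
- Listed GPs as a share of respondents = s × r / 0.15.
- Shift in an unweighted proportion = (s × r / 0.15 − s) × d.

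This takes respondents within each group as representative of that group, so it isolates the list component only.

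**Shift in percentage points for d = 20 points:**

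| s | r = 15% | r = 20% | r = 30% | r = 45% |
|---|---|---|---|---|
| 2% | 0 | 0.13 | 0.40 | 0.80 |
| 5% | 0 | 0.33 | 1.00 | 2.00 |
| 10% | 0 | 0.67 | 2.00 | 4.00 |

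For d = 10 the entries halve; for d = 30 they are multiplied by 1.5.

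- Middle case (s = 5%, r = 30%, d = 20): listed GPs are 0.05 × 0.30 / 0.15 = 10% of respondents, about 77 of 774. The shift is (0.10 − 0.05) × 20 = 1.0 point. Scaled to the register, 0.01 × 5,158 is about 52 physicians.
- Largest case (s = 10%, r = 45%, d = 30): listed GPs are 30% of respondents, about 232 of 774. The shift is (0.30 − 0.10) × 30 = 6.0 points. The other GPs would then respond at (0.15 − 0.045) / 0.90 = 11.7%, so listed GPs would have to answer almost four times as often.

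**Comparison with sampling error.** At n = 774 the 95% half-width is 1.96 × √(0.20 × 0.80 / 774) = 2.8 points for a proportion of 0.20, and 3.5 points for 0.50. With the finite-population factor (1 − 774/5,158) these become 2.6 and 3.2. Of the 36 combinations, four exceed 2.8 points: two at 3.0, one at 4.0 and one at 6.0.

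**Effect of weighting.** The estimate s × p(listed) + (1 − s) × p(other) brings this component to 0 if, within each group, response is unrelated to level 2 provision. The cost in precision follows from the weights:
- In the middle case they are 0.05/0.10 = 0.50 and 0.95/0.90 = 1.056. The variance factor is 0.10 × 0.50² + 0.90 × 1.056² = 1.03, so the interval widens by about 1%.
- In the largest case they are 0.10/0.30 = 0.333 and 0.90/0.70 = 1.286. The factor is 0.30 × 0.333² + 0.70 × 1.286² = 1.19, so it widens by about 9%.

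**The case against.** A reader might infer that academically linked practices are over-represented and that all replies are pooled with equal weight. The article supports neither statement. Every registered GP is invited, so the list contact adds nobody to the frame, and over-representation arises only if listed GPs respond at a higher rate. Equal weighting is a reading of silence: weighted frequencies are descriptive too, and their specification may sit in a full protocol or analysis plan that is not shown.

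Other points on that side also have force. Teaching practices are only an example of the lists. The address registers are described as still under development, so the lists may partly serve to reach GPs without a usable address, which would help coverage. The actions are introduced as conditional, although the same list contains the basic invitation to all GPs, so the condition cannot be taken at face value for every item.

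Nor can it be said that reaching 774 by this route makes the estimate worse overall. At 15% response, self-selection by interest in the topic may be larger and could run in either direction. GPs who answer because of an institutional tie might even dilute it.

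What remains is that a selective prompt is planned in a survey meant to describe the whole register, and that the article names no way of identifying who received it. That most assumed shifts lie below the sampling half-width limits the severity but does not remove the point, because a shift of this kind does not shrink as replies accumulate.

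**Conclusion.** The point holds as a conditional one. The extra contact may raise response among listed GPs; if they also differ in level 2 provision, the work package 1b frequencies move away from the register values. The size cannot be obtained from the article. Over the assumed ranges it runs from 0 to 6 percentage points, and it is 2 points or less for a list share of up to 5% and a difference of up to 20 points. These figures assume 15% overall response, list response of at most 45%, and respondents who represent their own group. The stronger reading, that the results are biased towards academic practices and that no adjustment will be made, goes beyond the text. Severity is low: this is a cheap improvement whose value depends on its being made before data collection.

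**What to change.** Before the survey opens, add one questionnaire item on teaching-practice or mailing-list status. It should ask something a GP can answer reliably, such as whether the practice teaches for the medical school. A separate survey link is not enough: it records the channel, and a listed GP can still answer through the general link.

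Report the main frequencies by that status, and with and without these respondents. Where the number of such GPs among the 5,158 is known under the same definition, with overlaps between lists removed, also show frequencies weighted to the register shares. A further reminder to all GPs is no substitute, as it would largely repeat the weekly reminders already planned.

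The cost is one extra item, a few additional table columns and slightly wider uncertainty for the weighted figures. The change deals only with the list contact. General self-selection at 15% response would remain and should still be acknowledged when the results are reported.

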### Dissemination and implementation

The results of the project will facilitate the nationwide optimisation of outpatient palliative care, as well as its administration. The findings may also be used to improve hospice and palliative care and propose structural changes to the legal framework. The empirically developed recommendations for optimising level 2 palliative care may be used to inform the legislative adaptation of level 2 palliative care. This would enable a rapid transfer into practice for the benefit of patient care, impacting a very large population. Good outpatient palliative care–and especially early palliative care–can allow patients to die at home and avoid hospitalisation and cost-intensive therapies; at the same time, it can lead to a higher quality of life and better symptom control at the end of life [15].

All project partners support the dissemination of the recommendations following project completion. To promote the accessibility and long-term safeguarding of the research data and results for the scientific community, the consortium will report comprehensively and transparently on the project and, regardless of the results, prepare national and international publications (with open access, where possible). Furthermore, the project team will make electronic research data (protected by data protection and copyright) available for secondary use in response to verifiably justified requests.

## Conclusion

The present study protocol explains the purpose, significance and scope of the mixed-methods study Polite, as well as the study design. The empirically developed recommendations that will be generated in this study are expected to optimise outpatient palliative care in Germany. The results may also initiate structural changes to the legal framework.

The authors’ goal of publishing the present study protocol is to promote research transparency beyond registration in the German Clinical Trials Register. Moreover, the study protocol may act as a point of reference for the Polite project team, the scientific community and other parties interested in the scientific and ethical aspects of the study. Finally, the publication of the study protocol may prevent unnecessary duplication.
